## Abstract

**Background:**

Working memory deficits are one of the core and most characteristic clinical features of cognitive impairment in schizophrenia. Cognitive training can improve the cognitive function of patients with schizophrenia. However, the overall and transfer effects of working memory treatment (WMT) require improvement. Numerous studies have confirmed that transcranial direct current stimulation (tDCS) enhances neuroplasticity in the brain, providing a new treatment approach for cognitive impairment in patients with schizophrenia. We hypothesize that a training mode combining “preheating” (tDCS, which changes the neural activity of working memory-related brain regions) and “ironing” (WMT) affords greater cognitive improvements than WMT alone. In addition, this study aims to examine the mechanisms underlying the superiority of tDCS combined with WMT in improving cognitive function in patients with schizophrenia.

**Methods:**

This study will include 120 patients with schizophrenia aged 18–60 years. The patients will be randomized into four groups: the study group (tDCS + WMT), tDCS group (tDCS + simple response training, SRT), WMT group (sham tDCS + WMT), and control group (sham tDCS + SRT). Patients will receive 20-min, 2 mA sessions of active or sham tDCS twice a day on weekdays for 2 weeks. Each stimulation will be immediately followed by a 1 − 2-min rest and 40 min of WMT or SRT. The primary outcome is cognitive function, measured using Repeatable Battery for the Assessment of Neuropsychological Status (RBANS) and some subscales of the MATRICS Consensus Cognitive Battery (MCCB). The secondary outcomes are other behavioral measures, variations in brain imaging, and serum levels of brain-derived neurotrophic factor (BDNF). All outcomes will be measured at baseline, post-treatment, and 3-month follow-up, except for brain imaging and BDNF levels, which will be measured at baseline and post-treatment only.

**Discussion:**

If tDCS combined with WMT results in significant improvements and prolonged effects on working memory, this method could be considered as a first-line clinical treatment for schizophrenia. Moreover, these results could provide evidence-based support for the development of other approaches to improve cognitive function in patients with schizophrenia, especially by enhancing WMT effects.

**Trial registration:**

Chictr.org.cn; ChiCTR2200063844. Registered on September 19, 2022.

**Supplementary Information:**

The online version contains supplementary material available at 10.1186/s13063-022-06776-x.

## Background

Schizophrenia is one of the most common severe mental disorders, and its etiology remains unknown. Cognitive deficits (CD), one of the core symptoms of schizophrenia, affect attention, memory, executive function, and social cognition. Among them, working memory deficits are one of the core and most characteristic of schizophrenia. These deficits are closely related to the social function, daily living ability, and academic performance of patients [1, 2].

Studies have confirmed that central control components play a fundamental role in the working memory system, which is primarily related to dorsolateral prefrontal cortex (DLPFC) function [3], but also involves the basal ganglia and hippocampus [4, 5]. An abnormal functional connection between the prefrontal lobe and other working memory-relevant areas has been hypothesized to underlie working memory deficits in schizophrenia [6, 7]. In addition, the level of brain-derived neurotrophic factor (BDNF), a protein critical for neural plasticity and synaptic signaling, was found to be decreased and closely related to impaired cognitive function in schizophrenic individuals, indicating its critical role in the pathological mechanism of schizophrenia [8–14].

Many studies have shown that repeated intensive and targeted cognitive training, such as cognitive remediation therapy (CRT), significantly improves cognitive deficits [15, 16]. Although several studies have shown that neuropsychological training methods such as CRT can significantly improve the cognitive function of patients with schizophrenia, the overall effect value is around 0.4, which is of moderate level. In particular, for working memory, the effect value was approximately 0.35. A recent systematic review showed that the overall effect of cognitive training was 0.38 and the effect on working memory was 0.29 [17]. Therefore, there is an urgent need to improve cognitive training, especially to increase the effect on working memory.

Studies have shown that cognitive training and sports rehabilitation can improve behaviors, and result in changes in the functioning and functional connections of the trained and related areas. In addition, these changes in brain plasticity are closely related to the persistence of the training effects [18]. The greater the neuroplasticity, the better the training effect and the longer the duration. Therefore, improving the training effect by altering neuroplasticity may be a promising direction for working memory treatment (WMT) [2]. Transcranial direct current stimulation (tDCS) is a safe electrophysiological method for improving neuroplasticity. Short-term tDCS can cause changes in local brain electrical activity and affect cognitive ability. Long-term repeated tDCS by long-term potentiation (LTP) or long-term depression (LTD) leads to continuous changes in the function or functional connectivity of local or related brain regions, ultimately resulting in changes in brain structure and function. One study suggested that a single tDCS (1–2 mA) can temporarily improve executive functions and working memory, as well as learning and memory capabilities in non-affected subjects. After stimulation with a current of 1.5 mA for 20 min, the excitability of the motor cortex was increased by 150% compared with baseline, and the effect lasted for 90 min [19]. A study in elderly subjects found that 10 min tDCS anode stimulation of the left inferior frontal gyrus significantly reversed aging-induced cognitive impairment, reduced bilateral hyperactivity in the prefrontal cortex and anterior cingulate gyrus, diminished wedge-shaped brain activation, and normalized the resting brain function connection mode [20]. A functional magnetic resonance imaging (fMRI) study of patients with schizophrenia found that tDCS stimulation of the left frontal lobe for 30 min resulted in significantly improved working memory performance 24 h post-treatment, a finding that was positively correlated with increased activation in the medial frontal cortex below the anode [21]. A study on tDCS combined with cognitive training found that the latter significantly improved cortical neuroplasticity [22]. Another study of healthy elderly subjects also found that bilateral tDCS of the prefrontal lobe combined with computer cognitive training significantly improved working memory performance. This study showed that during computer cognitive training, tDCS-induced bilateral changes in prefrontal excitability may improve age-related cognitive decline in elderly subjects [23]. These findings suggest that a combination of tDCS and working memory training may be a promising treatment to improve the working memory ability of patients with schizophrenia.

Therefore, we hypothesized that the training approach combining “preheating” (tDCS, which changes the activity of working memory-related brain regions) and “ironing” (WMT) will result in an enhanced effect. To date, no relevant studies have investigated whether or how this combined intervention improves cognitive function, especially working memory, in patients with schizophrenia.

This trial is the first to test the efficacy of the combination of tDCS and WMT on working memory and other cognitive functions in schizophrenia using a double-blind, randomized, controlled design. Numerous neuropsychological and neuroimaging assessments, as well as serum assays, will be performed to better evaluate the efficacy of this intervention. We hypothesized that this study will provide evidence for the greater improvement in cognitive deficits afforded by tDCS combined with WMT, especially for working memory deficits, while elucidating the neuroplastic changes that occur through this combined approach.

## Methods

### Study design

This is a double-center, double-blinded, randomized, controlled intervention trial. This study was registered under Chictr.org.cn (ChiCTR2200063844). This study will be conducted from 2022 to 2024 and reported in accordance with both the Consolidated Standards of Reporting Trials (CONSORT) statement and the CONSORT statement for non-pharmaceutical interventions [24, 25].

The primary objective of this trial is to investigate the facilitation (enhancement) effect of tDCS-induced neuroplasticity changes on the direct and migratory effects of WMT on cognitive function in schizophrenia. The secondary goals are to investigate the effects of tDCS and WMT on the brain plasticity and biological markers of patients with schizophrenia, and to examine the facilitation effect of tDCS on WMT-induced changes in brain plasticity and biological markers.

### Participants

This study has been approved by the Ethics Committees of Beijing Huilongguan Hospital and Chongqing Three Gorges Hospital Pinghu Branch and conformed to the Declaration of Helsinki (version 2004). The Standard Protocol Items: Recommendations for Interventional Trials (SPIRIT) checklist is detailed in an additional document available upon request, and the schedule of this study is presented in Fig. 1. All patients will sign a written consent to participate in the study after understanding its purpose and procedures.

**Fig. 1 Fig1:**
[figure not shown]
SPIRIT figure showing schedule of enrollment, intervention, and assessments of the study. Repeatable Battery for the Assessment of Neuropsychological Status (RBANS), MATRICS Consensus Cognitive Battery (MCCB), Wechsler Adult Intelligence Test Brief Version (WAIS-R), Positive and Negative Syndrome Scale (PANSS), Brief Negative Symptom Scale (BNSS), the Clinical Global Impression (CGI), Personal and Social Performance Scale (PSP), Temporal Experience of Pleasure Scale (TEPS), vocal emotion recognition test (VERT), facial emotion recognition test (FERT), Self-Esteem Scale (SES)

A total of 120 patients with schizophrenia will be recruited from Beijing Huilongguan Hospital and Pinghu Branch of Chongqing Three Gorges Hospital, according to the following inclusion criteria: diagnosis of schizophrenia according to the Diagnostic and Statistical Manual of Mental Disorders, 5th edition (DSM-V); age between 18 and 60 years; full education of at least 6 years (we ensure that the participants are able to read and understand the task instructions); single score on the Positive and Negative Syndrome Scale (PANSS) < 5 or total PANSS score < 22; evidence of cognitive impairment (the length of number backwards ≤ 6); and right-handedness (Edinburgh Handedness Assessment Scale). The exclusion criteria are as follows: history of an organic brain disorder or other severe organic disorder; diagnosis of substance abuse, as defined by the DSM-V; hearing or visual perception disorders; severe physical diseases or side effects of drugs; inability to carry out cognitive training; severe recession or impulsive excitement; lack of cooperation; pregnancy or lactation; and presence of foreign metal objects or cardiac pacemakers in the body that could prevent MRI scanning. Inclusion and exclusion criteria will be assessed using an electronic case report form (eCRF). Dropping criteria include failure to complete the training ten times in total and unable to continue to participate in the study due to disease relapse or worsening.

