### Sample size

The sample size was estimated based on the previous study reporting an effect size of 0.25 for observing the effect of CCRT on cognition [26]. With an alpha error estimate of 0.05 and power (1-β) of 0.90, 4 groups and 3 repeat measurements with a correlation among repetitive measures of 0.5 and nonsphericity correction of 1, a minimum sample size of 52 was required using G*Power 3.1.9.2 [27]. Accounting for the possibility of dropouts, the study adopts the block randomization to divide into groups with 8 patients in each block. The actual sample size of each group was 30 cases. Combining the clinical situations of each center, the Beijing and Chongqing centers were set to provide 80 and 40 patients, respectively.

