### Neuropsychological assessments

Cognitive function will be measured with RBANS and some subscales of the MCCB and the Wechsler Adult Intelligence Test Brief Version (WAIS-R). The primary evaluation indicators of a training effect on working memory are the spatial span and digital sequence subscales in the MCCB and the RBANS. Evaluation indicators of the migration effect are reasoning and problem solving ability evaluated by the maze test and social cognition ability determined by the vocal emotion recognition test (VERT) and facial emotion recognition test (FERT).

Clinical symptoms will be evaluated using the Chinese version of the PANSS, Brief Negative Symptom Scale (BNSS), and Clinical Global Impression (CGI). These will be assessed by four clinically trained senior physicians at each center.

Social function will be determined with the Personal and Social Performance Scale (PSP). Other scales employed are the Temporal Experience of Pleasure Scale (TEPS), Self-Esteem Scale (SES), and side effects scale*.*

The results from the above mentioned neuropsychological tests will be blindly assessed by raters who are unaware of the treatment the patients are receiving. Except for the WAIS-R, which will be assessed only once at baseline, the other scales will be assessed at three time points (baseline, post-treatment, and 3-month follow-up).

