This study has some limitations that must be addressed. First, the enrolled participants are not fully representative of a patient population with other comorbidities and considerable treatment heterogeneity. Therefore, we chose strict inclusion, exclusion, and dropping criteria to reduce the effects of confounding variables and to render the trial more accurate and realistic. Second, there may be challenges regarding the participants’ reaction to the trial, e.g., if the participant believes they are receiving sham treatment or if the treatment is too uncomfortable or too tiring. It is not clear whether participants will be able to distinguish between the real and sham treatments and the impact this may have on attrition rates.

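### The total-PANSS entry condition of below 22 cannot be met on the usual 30-item form and, joined by 'or', sets no ceiling on any scoring, so symptom eligibility rests on the single-score condition alone

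*Protocol article*

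**What the plan says.** The inclusion criteria in the protocol article (Methods, Participants, in the text after Fig. 1) contain one numerical limit on symptoms: "single score on the Positive and Negative Syndrome Scale (PANSS) < 5 or total PANSS score < 22". Eligibility is to be checked through the eCRF.

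The Neuropsychological assessments section says that the Chinese version of the PANSS is used. No section gives its number of items, the item anchors, the range of the total or any subscale cut-off.

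Severity is otherwise limited only in words. The exclusions cover patients who cannot do the training, and also "severe recession or impulsive excitement; lack of cooperation". The limitations paragraph of the Discussion describes the criteria in general terms: "we chose strict inclusion, exclusion, and dropping criteria to reduce the effects of confounding variables".

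**The concern.** A cut-off of 22 on a score called the PANSS total looks too low for that instrument to reach. If so, half of the only numerical symptom criterion does nothing, and the number or its label is wrong.

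The connective raises a separate question. A severity limit normally keeps out patients above it. Under 'or', a patient who meets one condition need not meet the other, so the total condition cannot keep anyone out.

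What is at stake is whether the rule coded in the eCRF is the one the sponsor meant, and whether the trial can later describe its population by a symptom limit that actually operated.

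**Working it through.** **Inputs from the document.** Single score below 5; total below 22, so the highest qualifying total is 21; connective 'or' (all from Participants).

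**Assumption, not in the document.** The usual PANSS form has 30 items scored 1 to 7. The alternatives tried are 30 items scored 0 to 6, and shorter scales with items scored from 1.

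**The plan's own figure.** The cut-off of 22 has no derivation to reproduce. The only computed figure in the article is the sample size: "a minimum sample size of 52 was required using G*Power 3.1.9.2". It reproduces for the within-between interaction of a repeated-measures ANOVA. With f = 0.25, 3 measurements and correlation 0.5, λ = 0.25² × 52 × 3 / (1 − 0.5) = 19.5. With df1 = 3 × 2 = 6 and df2 = 48 × 2 = 96, power is 0.915. No PANSS quantity enters, so the sample size does not depend on this point.

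**Step 1: can a total below 22 occur?** Lowest total = number of items × lowest anchor.

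| Score | Lowest total | Highest total | Below 22 attainable? |
|---|---|---|---|
| 30 items, 1–7 | 30 | 210 | No |
| 30 items, 0–6 | 0 | 180 | Yes |
| 16 items, 1–7 | 16 | 112 | Yes |
| 14 items, 1–7 | 14 | 98 | Yes |
| 7 items, 1–7 | 7 | 49 | Yes |

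On the usual form the gap is 30 − 21 = 9 points. With items scored from 1, a total of 21 or less needs at most 21 items.

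**Step 2: when does the total condition admit anyone extra?** Read the item condition as every item below 5. The patient with the lowest total who fails it has one item at 5 and the other k − 1 items at 1, so the total is 5 + (k − 1) = k + 4. This is at most 21 only if k ≤ 17. With 18 to 21 items the total condition can be met but adds no patient. With 17 or fewer it adds patients who fail the item condition. On 30 items scored from 0 it also adds patients: one item at 5 and the rest at 0 gives a total of 5.

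**Step 3: does the total condition ever act as a ceiling?** Under 'or', a patient with every item at 4 or lower is admitted whatever the total. On 30 items the total can then reach 30 × 4 = 120, on 1–7 and on 0–6 scoring alike. So 22 is never a ceiling. This follows from the connective and does not need the assumed floor of 30.

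**Step 4: what the item condition means.** The natural reading is that every item must be below 5. If one item below 5 were enough, on the 1–7 form only a patient with all 30 items at 5 or more (total at least 30 × 5 = 150) would fail, and the criterion would exclude almost nobody. The wording does not settle this, but the second reading would make the rule pointless.

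**The case against.** The strongest objection is that the impossibility rests on a scale range the document does not give. That stands. With items scored from 0, or with a subscale behind the 22, the condition can be met, so the claim is conditional. The text does name the total score, however, and the absence of a ceiling under 'or' holds on every scoring.

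A second objection is that a journal article leaves item-level detail to the full protocol and the eCRF. That is fair for the every-item question, which is a minor part of the point. It does not cover the 22, which is stated, not left out.

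A third is that severity is controlled elsewhere. This also stands in part: the patient with 30 items at 4 is an arithmetical extreme and must still pass the qualitative exclusions.

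A reader might infer more than the document supports:

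- **That the rule misses the intended population.** No section states an intended symptom severity. The Discussion sentence about strict criteria is general and does not mention the PANSS.
- **That nobody could be enrolled.** That would follow on the usual form if 'and' were written. The text says 'or', so patients enter through the item condition.
- **That the rule adds noise or raises relapse-related loss.** The document gives no figure for either. Wider severity would not bias a randomised comparison, and 120 patients are planned against a computed minimum of 52.
- **That the two centres will apply it differently.** Both use the eCRF under one project management team, so divergence is possible but not shown.

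**Conclusion.** The point holds in limited form. On the usual 30-item PANSS scored 1 to 7, which is an assumption, a total below 22 is out of reach by 9 points and the condition has no effect. It is attainable only with items scored from 0 or on a subscale of 21 or fewer items.

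Without that assumption, it remains true that under 'or' the total condition sets no ceiling. Numerical symptom eligibility therefore has no limit beyond the single-score condition, which most naturally means every item and allows totals up to 120 on 30 items.

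Either the cut-off, the score it refers to or the connective is mis-stated. The document does not show which. This is an error in an operative eligibility rule and should be corrected before recruitment. It does not threaten the validity of the randomised comparison, block enrolment or change the sample size.

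**What to change.** Before the first patient, reconcile the criterion on three points:

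1. Which PANSS score (total or a named subscale) and which scoring convention the 22 refers to.
2. Whether the item limit applies to every item.
3. Whether the two conditions are joined by 'and' or 'or'.

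Then code the reconciled rule as an eligibility check in the eCRF, identical at both centres. The threshold itself is for the sponsor's clinicians to set; none is proposed here.

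The cost is a one-line amendment and one eCRF edit check. The Trial status section says that recruitment had not yet begun at this protocol version, so at that stage no enrolled patient would be affected.

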### Randomization and blinding

Patients will be randomly divided at a ratio of 1:1:1:1 and assigned to one of the following four groups: study group (tDCS + WMT), WMT control group (tDCS + simple response training, SRT), tDCS control group (sham tDCS + WMT), and placebo control (sham tDCS + SRT). Block randomization will be performed in R (The R Foundation, Vienna, Austria) and carried out in 15 blocks of 8 participants. Each patient will be randomly assigned to the baseline group. To eliminate measurement bias, no member of the trial knew which group each patient will be assigned to, except for the caregivers who performed the tDCS treatment. Blinding will be resolved only when urgent treatment is required. Thus, the participant will be managed as off-trial.

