### Group interventions

#### *The study group (tDCS* + *WMT)*

Based on previous findings [28, 29], we will apply tDCS at 2 mA for 20 min each, with two stimulations per day separated by 3–4 h. Stimulation will be performed 5 days per week for two consecutive weeks, for a total of 20 stimulations.

We will administer tDCS using a battery-driven stimulator (EM8060, Wuhan YiMai Technology Co., Ltd., Hefei City, China) in Beijing center and a-tDCS (ActivaDose® II, ActivaTeKTM Inc., Gilroy, CA) in Chongqing center. A rectangular anodal electrode will be attached to the left DLPFC (F3 position, according to the International 10/20 system), and a rectangular cathode will be attached to the orbitofrontal cortex. The stimulation area will be wet with saline before treatment.

Each 20-min tDCS period will be immediately followed by a 1–2-min rest and 40 min of WMT (Fig. 2). The WMT tool is a computer training system based on theoretical models of working memory and cognitive processing. It was self-developed and validated in preclinical research [30]. This training employs the most typical working memory paradigm; that is, subjects try to memorize a series of continuous items (including numbers, words, and pictures) of random (unfixed) length, and judge the order of the 2–4 items presented at the end. Ten WMT sessions will be performed per week for two weeks, for a total of 20 WMT sessions.

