### Statistical analysis

Analyses will be performed according to the intent-to-treat (ITT) principle. Descriptive analysis will be performed on the data collected during each assessment at baseline, post-treatment, and the 3-month follow-up. The median and range describe continuous variables, and the frequencies and percentages describe qualitative variables.

Statistical significance will be set at *P* < 0.05, and corrected for multiple comparisons, when needed. To assess our primary endpoint criterion, that is, changes in cognitive performance, the outcomes at the three time points will be compared using a repeated-measures analysis of variance (ANOVA) with time (baseline, post-treatment, and 3-month follow-up) and group (tDCS + WMT, tDCS + SRT, sham tDCS + WMT, and sham tDCS + SRT) as factors. Further comparisons between the two groups can show the simple tDCS effect, simple WMT effect, and promoting effect of tDCS on WMT. Sensitivity analyses will be used to explore the effect of missing data due to loss to follow-up and dropout.

In cases where the data do not satisfy the assumption of normal distribution, the non-parametric Mann–Whitney *U* test will be used to compare the performance improvement between the four groups. SPM will be used to analyze imaging data to detect changes in brain function caused by cognitive training.

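### The rules that drop randomised patients or place them off-trial are not reconciled with the intent-to-treat analysis, and dropping after randomisation does not reduce confounding

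*Protocol article*

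**What the plan says.** Four places in the protocol article bear on the point.

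- **Methods, Participants** (paragraph after the Fig. 1 legend): "Dropping criteria include failure to complete the training ten times in total". The second criterion is being "unable to continue to participate in the study due to disease relapse or worsening". The planned course is given under the study group's interventions: "for a total of 20 WMT sessions". I read the first criterion as fewer than ten of 20 sessions. Both criteria can be met only after randomisation.
- **Methods, Randomization and blinding**: "Blinding will be resolved only when urgent treatment is required", followed by "Thus, the participant will be managed as off-trial".
- **Methods, Statistical analysis**: "Analyses will be performed according to the intent-to-treat (ITT) principle". The primary analysis is a repeated-measures ANOVA over baseline, post-treatment and 3 months in four groups. Sensitivity analyses are planned for data missing through loss to follow-up and dropout.
- **Discussion**, limitations paragraph: "we chose strict inclusion, exclusion, and dropping criteria to reduce the effects of confounding variables".

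No section says that a dropped or off-trial patient is excluded from the analysis. None says that such a patient is still assessed and analysed as randomised.

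**The concern.** Intent-to-treat requires that every randomised patient be analysed in the assigned arm, and in practice that outcomes be sought from patients who stop early. The article declares the principle but also has rules that take patients out of the trial for low adherence, for relapse or worsening that prevents continuation, and after unblinding for urgent treatment. It does not say how the two fit together.

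The Discussion makes this more than a missing detail. It lists dropping beside inclusion and exclusion as a way to limit confounding. Inclusion and exclusion act before randomisation and leave the comparison intact. Dropping acts afterwards, on events that the assigned treatment or the patient's course may influence. Randomisation has already balanced confounders in expectation, so selecting on later events cannot improve that balance and may disturb it. The stated rationale also makes sense only if dropped patients leave the data, which is the reading that does not fit intent-to-treat.

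At stake is the between-arm comparison of cognitive change. A score not collected at post-treatment or 3 months cannot be recovered by any later analysis.

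**Working it through.** **1. The plan's own figure.** The Sample size section gives a minimum of 52, from effect size 0.25 (taken as Cohen's f), alpha 0.05, power 0.90, 4 groups, 3 measurements, correlation 0.5 and nonsphericity correction 1. For the group-by-time interaction, λ = f²·N·m/(1 − ρ) = 0.0625 × 52 × 3 / 0.5 = 19.5, with df 6 and (52 − 4) × 2 = 96. Power is 0.915, and 52 is the smallest multiple of 4 that reaches 0.90, so the figure reproduces. (The within-factor and between-factor versions give 36 and 156.) With 120 patients the same test has power above 0.999; at 30% loss (N = 84) it is 0.994. N falls to 52 only at 1 − 52/120 = 57% loss. On the plan's own assumptions for this test, the issue is bias, not power.

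**2. The passages side by side.**

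| Question | Dropping criteria | Unblinding | Statistical analysis |
|---|---|---|---|
| Does study treatment stop? | implied | implied by off-trial | not addressed |
| Do assessments stop? | not stated | not stated | dropout is named as a source of missing data |
| Does the patient leave the analysis? | not stated; the Discussion's rationale points that way | not stated | intent-to-treat says no |

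The third row is where the sections fail to agree. A conventional repeated-measures ANOVA uses only patients with all three visits. If it is run that way, patients without later scores leave the primary analysis whatever the declared principle.

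**3. Size of the possible bias.** Let p be the dropped share of an arm, R the mean of retained patients, D the mean dropped patients would have had, and δ = R − D. The full-arm mean is (1 − p)R + pD = R − pδ, so analysing retained patients overstates the arm's mean by pδ. The between-arm bias is p₁δ₁ − p₀δ₀, which is (p₁ − p₀)δ when δ is common to both arms.

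The article gives no dropout rates. Assume p₁ = 10–20%, p₀ = 5% and δ = 0.5–1.0 SD:

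- lowest: (0.10 − 0.05) × 0.5 = 0.025 SD
- highest: (0.20 − 0.05) × 1.0 = 0.15 SD
- equal shares and equal δ: 0
- equal shares, unequal δ, for example 10% in both arms with δ of 1.0 and 0.5: 0.10 × (1.0 − 0.5) = 0.05 SD

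For scale, the Background quotes effects of cognitive training of 0.38 overall and 0.29 on working memory. The range is 0.025/0.38 = 7% to 0.15/0.29 = 52% of those. They are not effects of adding tDCS to WMT, so this is only a yardstick.

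**4. Simulation check (assumed inputs).** No true effect, change-score SD 1, 30 per arm, dropped patients left out, and dropping correlated 0.3 to 0.7 with poor outcome, equally in both arms.

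| Dropped | Between-arm bias (SD) | Two-sided type I error |
|---|---|---|
| 10% v 10% | about 0 (each arm's mean 0.06–0.14 too high) | 0.05 |
| 20% v 10% | 0.05–0.11 | 0.053–0.069 |
| 30% v 10% | 0.09–0.21 | 0.061–0.112 |

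If dropping is unrelated to outcome, the bias is zero.

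**The case against.** A reader might infer that the article flatly contradicts its intent-to-treat statement and removes poor outcomes selectively. The text does not carry that far.

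- Dropping and off-trial may mean only that treatment or active participation ends. No section says assessments stop or that these patients are excluded, and Data collection and follow-up plans calls to limit loss. This stands: the conflict is inferred from the rules and their rationale, not stated.
- The planned sensitivity analyses treat dropout as missing data, which is not silent removal. This stands in part: such analyses can probe the effect of missing scores but cannot replace scores never taken.
- The relapse criterion covers only patients unable to continue, not everyone who relapses. Ten sessions is an adherence threshold whose link to poor cognitive outcome is not shown. No frequency of unblinding is given. This stands.
- Session lengths and frequency are the same in every arm, so unequal dropping is not established. This stands. The article does mention headache, irritability and opting out for intolerance, describes SRT as free of working-memory load, and calls the effect on attrition unclear. Differences by arm are therefore plausible, but neither their size nor their direction is known.
- A condensed article may leave analysis sets to a fuller document. That is fair for set definitions. It does not cover the Discussion's printed rationale, which is wrong as it stands. Whether a patient is assessed after stopping is also trial conduct, which an analysis plan cannot restore afterwards.

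**Conclusion.** The concern holds as a failure to reconcile. The dropping criteria and the off-trial rule are left unconnected to the declared intent-to-treat principle, and the claim that dropping reduces confounding is wrong for post-randomisation events. Bias in the group comparison follows only under two conditions together: the patients are not assessed, or are omitted by an ANOVA that needs all visits; and dropping differs by arm, or relates to outcome differently by arm.

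The size is unknown. The 0.025–0.15 SD range rests wholly on assumed dropout shares and an assumed outcome gap, and it is about zero if dropping is equal and similarly selective. The documents do not establish that poor outcomes are being removed, nor which arm would gain.

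**What to change.** Amend the protocol as follows.

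1. State that a patient who meets a dropping criterion, or is unblinded, remains in the trial for assessment unless consent is withdrawn, is invited to the post-treatment and 3-month assessments, and is analysed in the randomised arm.
2. Name a primary model that keeps patients with incomplete visits, for example a mixed model for repeated measures. This supports item 1 and does not replace it, since a model can use only the scores that were collected.
3. Use the ten-session threshold only to define a secondary per-protocol set.
4. Take dropping criteria out of the confounding rationale in the Discussion.

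The clinical triggers for stopping treatment stay as they are; the change concerns assessment and analysis only. The cost is a short amendment and a few extra visits. The Trial status section says recruitment has yet to begin, so at that protocol version no outcome data would have been lost.
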